**List of Abbreviations**

| CA | California |
| --- | --- |
| CFR | Code of Federal Regulations |
| CAD | Coronary Artery Disease |
| CAT | Computed Axial Tomography |
| C.I. | Confidence Interval |
| COPD | Chronic Obstructive Pulmonary Disease |
| CT | Computed Tomography |
| ED | Emergency Department |
| F | F Distribution |
| FN | False Negative |
| FP | False Positive |
| GCP | Good Clinical Practice |
| GCS | Glasgow Coma Scale |
| HIPPA | Health Insurance Portability and Accountability Act of 1996 |
| ICI | Intracranial Injury |
| IRB | Institutional Review Board |
| ITP | Idiopathic Thrombocytopenia |
| LOC | Loss of Consciousness |
| K | Kappa statistic |
| mGray | miliGray |
| MRI | Magnetic Resonance Imaging |
| N | Number (typically refers to subjects) |
| NEXUS | National Emergency X-radiography Utilization Study |
| NIH | National Institutes of Health |
| PHS | Public Health Service |
| PI | Principal Investigator |
| P_L_ | Lower Confidence Limit |
| P_u_ | Upper Confidence Limit |
| QA | Quality Assurance |
| QC | Quality Control |
| TN | True Negative |
| TP | True Positive |
| UCLA | University of California, Los Angeles |
| UCSF | University of California, San Francisco |
| US | United States |
| X | Number (typically refers to subject related events) |

**Protocol Summary**

**1. SPECIFIC AIMS**

Radiographic imaging can provide information that is crucial in managing victims of blunt trauma. However, liberal and indiscriminant imaging is expensive, can delay critical interventions, and unnecessarily exposes patients to ionizing radiation and its potential for lethal malignant transformation.

Considerable benefit could be realized by identifying clinical criteria that reliably classify the risk of specific injuries in blunt trauma patients. Patients identified as “no risk” by such criteria would not harbor specific forms of injury, and would receive no benefit from radiographic evaluation for such injuries. These patients could safely be spared the expense and radiation exposure associated with such imaging.

The purpose of this project is to identify and validate the use of clinical criteria to stratify the risk of specific injuries among blunt trauma patients. This proposal specifically addresses the use of such criteria in assessing patients for intracranial injuries, where our previous work suggests that a decision instrument, composed of a limited number of clinical criteria, can reliably identify blunt head injury victims who have “no risk” of significant brain injury, and therefore no need for computed head tomography. We estimate that nation-wide implementation of this decision instrument could safely reduce tomographic imaging of blunt head injury victims by more than 12%, and reduce annual radiographic charges by $90 million, while simultaneously expediting trauma care and decreasing radiation exposure and its associated risk of radiation-induced malignancy.

The specific aim of this proposal is reduce computed head tomography by validating the ability of a previously developed decision instrument to reliably identify blunt head injury victims who have no risk of intracranial injury requiring neurosurgical intervention, and who can subsequently be safely spared tomographic imaging. This goal will be accomplished by confirming the following two hypotheses:

I - Blunt trauma victims have no risk of intracranial injury requiring neurosurgical intervention, and hence no need for imaging, if they exhibit all of the following characteristics: 1 - No evidence trauma skull fracture; 2 - No scalp hematoma; 3 - No neurological deficits; 4 - Normal level of alertness; 5 - Normal behavior; 6 - No persistent vomiting; 7 - No coagulopathy; 8 - Age less than 65 years.

II - Implementation of a decision instrument that omits computed tomographic head imaging of blunt trauma patients who exhibit all of these criteria will reduce the number of computed head tomographs without missing any intracranial injuries that require neurosurgical intervention.

These hypotheses will be tested in a nationwide prospective multicenter study. The study will document the presence or absence of each criterion, as well as the presence or absence of intracranial injury in a cohort of blunt head injury victims. This information will be used to calculate the sensitivity, negative predictive value and specificity of the overall decision instrument. Validating the sensitivity of the decision instrument with high statistical confidence requires evaluations on 368 intracranial injury victims who require neurosurgical intervention, which in turn could require evaluations on as many as 31,000 blunt head injury patients.

Reductions in computed tomography will be determined by counting the number of head tomographs performed on “no risk” patients. Reductions in charges and radiation exposure will be determined by respectively summing radiographic charges and life-time decreases in radiation morbidity and mortality for all “no risk” cases.

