In a two-phase observational study, Madden attempted to isolate a set of selective criteria capable of detecting all significant intracranial injuries, while simultaneously reducing the overall need for computed tomography. In the first derivation phase, 51 clinical variables were prospectively evaluated on patients undergoing head CT. Regression analysis, performed on subsets of these variables, was used to identify the combination of criteria that correlated highest with the presence of injury. Ten variables were subsequently identified as potential low risk criteria. In phase two of the study, these low risk criteria were applied to a second cohort of 273 patients. Five patients had false negative clinical screens, defined as the need for admission despite low risk stratification. Of these five, three had linear skull fractures, one had a small epidural and one had a small amount of subarachnoid blood. No patients with low risk criteria required operative intervention [29].

More recently, Haydel proposed guidelines for selective imaging of patients who had sustained LOC [62]. Unfortunately, the validation phase of the study, conducted at a single institution, contained only 909 total head injury victims, and contained too few patients with significant intracranial injuries to allow sensitivity to be assessed with an acceptably narrow 95% confidence interval. Furthermore, the study used any acute CT abnormality as a primary outcome measure, ignoring the fact that many of these abnormalities are clinically insignificant. Finally, the rule has low specificity and it is unclear whether it is capable of reducing the overall use of tomographic imaging [63]. One of the criteria in particular, injury above the clavicles, was only assessed in patients already selected for tomographic imaging. It is likely that this criterion would lead to an increase in the overall use of head CT imaging if it were used to guide imaging of all blunt trauma patients. These limitations, have severely hampered the acceptance of these guidelines among emergency medicine practitioners [64].

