In a Canadian study, Stiell, *et al*, employed more rigorous methodology in developing a guideline for imaging of adult blunt trauma patients who have sustained head injuries. This guideline recommends imaging for patients who exhibit any of the following five high risk factors: age 65 years or greater, persistent abnormal GCS scores (<15 for more than 2 hours), suspected open skull fracture, any sign of basal skull fracture, or persistent vomiting (two or more episodes). The criteria in this derivation study identified all cases requiring neurosurgical intervention, but the 95% confidence interval associated with this sensitivity were relatively wide (92 – 100%). This decision instrument also identifies “medium risk factors” (dangerous mechanism of injury, amnesia before impact > 30 minutes) that can be used to identify clinically significant injuries with 98.4% sensitivity (95% CI: 96 – 99%). The authors indicate that their decision rule would have advised imaging in only 54% of their blunt head injury population. However, many of the enrolled patients were followed clinically and never received imaging. The authors do not reveal how many of these patients would require imaging under the decision instrument, nor whether the instrument would actually decrease scanning among patients currently selected for imaging [63].

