Our work also suggests that the relatively small sample size used in the Canadian study may have led to overly optimistic results. In particular, the five “high risk” factors identified by the Canadian study (age 65 years or greater, persistent abnormal GCS scores, suspected open skull fracture, any sign of basal skull fracture, or persistent vomiting), were found in only 869 of the 917 intracranial injury cases identified in our study. This equates to a sensitivity of 94.8% in detecting significant intracranial injury. Fourteen of the missed injury cases required neurosurgical intervention, and provide concrete evidence that the Canadian “high risk” criteria are not 100% sensitive in detecting these important lesions. Errors in the Canadian instrument likely result from the fact that a GCS of 15 is not equivalent to a normal neurological exam. Patients can exhibit subtle neurologic impairments such as altered level of alertness and behavioral abnormalities, and still attain a “normal” GCS score of 15. It is also likely that the additional criteria identified as being important in our work (scalp hematoma and abnormal behavior), are important subtle indicators of intracranial injury that are essential in producing a decision instrument with high sensitivity. Because we did not collect specific information on traumatic amnesia and injury mechanism, we are unable to assess the overall sensitivity of the Canadian instrument, and whether it would decrease imaging among our cohort.

Because of the previously mentioned issues, there is a need for prospective validation of the proposed decision instruments for selective tomographic imaging of blunt trauma victims. We therefore propose an observational study that will document the clinical presentation of blunt head injury victims prior to computed tomographic imaging and combine this observational data with CT results and need for neurosurgical intervention to determine whether combinations of clinical criteria can reliably detect all patients at risk of significant intracranial injuries, reliably exclude injury in low risk patients, and reduce the overall number of CT evaluations in blunt head injury victims.

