**4.3.2 - Data Collection and X-ray Ordering**

**4.3.2.1 - Patient Entry**

Every blunt trauma victim presenting to a study center will undergo a clinical evaluation. The examining physician will determine if computed head tomography is indicated, using whatever criteria they deem appropriate. Physicians will be informed that it is not currently possible to exclude intracranial injuries in patients who present with any of the risk criteria, and they will be encouraged (but not required) to obtain radiographic imaging on any blunt head trauma victims presenting with one or more of these criteria (see Appendix - B for a sample data entry screen and listing of criteria). Conversely, the clinicians will also be informed that the criteria have yet to be proven reliable, and that imaging should be considered for any patient suspected of harboring an intracranial injury. There will be no formal requirement to obtain or exclude tomographic imaging of any patient. Physicians will be free to order or omit computed head tomography at their discretion.

Data capture will occur each time a request for computed head tomography is made. Tomographic imaging will be performed only after a computer generated radiographic request is presented to the tomography technician. Tomographic requests will not be available until the examining physician completes a full assessment and records the survey responses. This strategy assures that a complete data set will be captured on each patient prior to radiographic imaging. Several of the participating sites use computer based automated entry systems to order radiographic imaging. Previous experience reveals that these systems can be easily modified to adhere to our study protocols, including the collection and de-identification of survey data and imaging results. Because these systems are automated, they do not print imaging requests, but can be programmed to issue requests only after survey data has been entered. Our two prior studies reveal that these systems are easily configured, very reliable, and easier to maintain than standard systems using printed requests.

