It is possible that clinicians may not be able to evaluate individual criteria in some patients. For example, it may not be possible to perform a detailed neurological exam and assess motor strength in an individual who has multiple extremity fractures and is unable to cooperate. Clinicians can indicate such occurrences by designating the presence or absence of the individual criterion as “unknown”. The overall decision instrument will treat these “unknown” responses as abnormal responses. Individual risk criteria will be classified as absent only if they can be tested and found to be absent. Consequently, the decision regarding the ultimate need for tomography is based on measuring individual criteria and determining that they are *all absent* in a given individual. If a patient exhibits any of the criteria, or if one or more of the criteria cannot be assessed, the individual will be labeled positive by the decision instrument. Such patients may harbor a significant intracranial injury and should be considered candidates for tomographic scanning. Clinicians are not to use the “unknown” designation in lieu of an adequate evaluation. Our experience with the cervical spine and head injury derivation studies reveals that study physicians use this designation appropriately.

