
**4.3.9.2 - Specificity**

Bias in the specificity measurements could result from misclassification of subjects, or from selection bias due to non-random exclusion of patients from the study. Such exclusions could produce a study population that does not represent trauma patients in general. If many patients omitted from the study have "no-risk" criteria then our measure of specificity will be too low; the converse is also possible. It is impossible to determine the direction of possible bias in our specificity measurements. Our specificity estimates, even if biased, would be very unlikely to change enough to substantially alter our conclusions. For example, if clinicians ordered tomography only for seriously injured patients, most of whom have at least one of the risk criteria, then the number of uninjured patients labeled negative by the criteria will be small and the specificity will be low. On the other hand, if clinicians order large numbers of tomograms on patients with no complaints, then the number of uninjured patients labeled negative by the criteria will be large and the specificity will be high. The first scenario would result in erroneously low estimates of cost savings using criteria, while the second scenario would over estimate savings, however, neither scenario would alter the number of patients who have injury and are identified as such by the criteria. Thus errors in specificity may affect cost-saving estimates but will have little influence on the validity of selective criteria. Furthermore, data collection at the Pittsburgh site will include imaged as well as un-imaged cases, and will provide a means of estimating the specificity of the instrument when applied to all blunt head injury patients.

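### The planned CT-reduction count is a gross figure among patients already selected for CT and does not support the protocol's claims about overall imaging

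*Protocol*

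**What the plan says.** **The estimator.** Section 1 (Specific Aims): "Reductions in computed tomography will be determined by counting the number of head tomographs performed on" no-risk patients. Charge and radiation savings are summed over those same cases.

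**The cohort.** Section 4.3.2.1: "Data capture will occur each time a request for computed head tomography is made". Patients evaluated but not sent for CT are outside the main study.

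**The claims.** Hypothesis II reads: "Implementation of a decision instrument that omits computed tomographic head imaging of blunt trauma patients who exhibit all of these criteria will reduce the number"; head CTs are what is counted. The Background goes further and asks whether the criteria can "reduce the overall number of CT evaluations in blunt head injury victims". The Specific Aims project a cut of more than 12% under nationwide implementation, and the Background puts nearly $90 million a year on general use of the instrument.

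**What a positive result means.** Section 4.3.3 says of patients with any criterion present or not assessable: "Such patients may harbor a significant intracranial injury and should be considered candidates for tomographic scanning". Section 4.3.2.1 encourages, but does not require, imaging of anyone with a criterion.

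**Un-imaged patients.** Sections 4.3.2.2, 4.3.3.1 and 4.3.4 and Appendix E describe criteria assessment of 368 consenting un-imaged patients at the UCLA centre, for work-up bias. Section 4.3.9.2 instead says that "data collection at the Pittsburgh site will include imaged as well as un-imaged cases", for estimating specificity. Neither source is linked to the CT-reduction count.

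**The concern.** A count of scans performed on low-risk patients cannot be negative. If applying the instrument led clinicians to scan patients they now leave un-imaged, total imaging could rise while the planned outcome still reported a reduction. The criteria in Appendix C are broad enough for this to matter: any hematoma over the calvarium, impaired clotting including that due to aspirin, or age 65 or more makes a patient positive.

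The Background raises a similar gap in two other rules. Of one rule, with a criterion assessed only in patients already chosen for imaging, it says: "It is likely that this criterion would lead to an increase in the overall use of head CT imaging". Of the Canadian rule, under which many patients were followed without imaging, it says: "The authors do not reveal how many of these patients would require imaging under the decision instrument".

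At stake are the reduction half of Hypothesis II and the charge and radiation figures, all of which rest on this one-sided count.

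**Working it through.** **Step 1. Reproduce the protocol's figure.** From the derivation study (section 3.1): 13,728 patients with CT ordered, 1,752 correctly classified low risk, and 16 important injuries among those classified low risk.

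- Low-risk imaged / all imaged = (1,752 + 16) / 13,728 = 12.88%, which gives the stated 12.9%. (1,752 / 13,728 alone is 12.76%.)
- Charges: 12.9% of $750 million = $96.8 million; 12% gives $90.0 million. The stated figure of nearly $90 million is the same gross reduction, rounded down.

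Both denominators are scans already performed. Neither contains un-imaged patients.

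**Step 2. Write the net change.** Let f be the share of all blunt head injury patients who are imaged, r = (1-f)/f the ratio of un-imaged to imaged, and q the criterion-positive share of the un-imaged. If every positive patient is scanned and every negative one is not:

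net reduction, as a share of current CT volume = 0.129 - r × q

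If the instrument only removes scans, the second term is absent and the reduction is 12.9%.

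**Step 3. Break-even.** Setting the net to zero gives q = 0.129 f/(1-f). The protocol gives neither f nor q, so f is an assumption shown over a range.

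| f (assumed) | r | q at which the saving is cancelled |
|---|---|---|
| 30% | 2.33 | 5.5% |
| 50% | 1.00 | 12.9% |
| 70% | 0.43 | 30% |
| 80% | 0.25 | 52% |

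Above f = 1/1.129 = 89%, q would have to exceed 100%, so the net cannot turn negative.

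**Step 4. Illustrations (f and q assumed).**

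- r = 0.5, q = 10%: 12.9 - 5.0 = +7.9%
- r = 1, q = 10%: 12.9 - 10.0 = +2.9%
- r = 1, q = 25%: 12.9 - 25.0 = -12.1%

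**Step 5. Scale in this study.** With 31,000 imaged patients, 0.1288 × 31,000 is about 3,990 scans counted as avoided. About the same number of added scans would cancel them.

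**Step 6. What the un-imaged cohort could tell us.** With 368 un-imaged patients and 37 positive (10%), the exact 95% interval for q is 7.2% to 13.6%. That is useful precision, but at f = 50% it still includes the break-even value of 12.9%. Turning q into a net figure also needs f, and hence a count of all un-imaged patients at the site.

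**The case against.** The strongest reply is that Hypothesis II describes an instrument that omits scans, and the Specific Aims speak of sparing patients imaging. Under that use nothing is added, the count is the right estimator, and its inability to go negative is no defect. Nor does the protocol require a scan in positive patients: they are candidates, and imaging is encouraged only. This stands. A reader might infer that the saving is overstated outright, or that the instrument would probably raise total imaging. The documents support neither, because both depend on two-way use and on f and q, which are not given. The reply does not rescue the wider claims, however, because the protocol never limits use to ruling out.

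A reader might also infer that the protocol commits exactly the fault it finds in other rules. That goes too far. The sentence on the Canadian rule goes on to ask whether scanning would fall among patients currently selected for imaging, which is what the planned count measures. The other criticism concerns one criterion of another rule.

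Section 4.3.9.2 does concede that savings could err in either direction, but it attributes this to which patients clinicians choose to scan and says nothing of added scans.

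It is also fair to say that a net estimate would not come wholly from data in hand. Un-imaged patients are recorded only with consent and at one centre, no log of non-consenters is described, and clinicians are encouraged during the study to image positive patients, which would lower q. Nor can section 4.3.9.2 simply be declared wrong about the site: the list of centres in Appendix A is not in the text at hand, and a further site may be meant.

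Finally, section 4.3.7 does not list CT reduction among its primary or secondary outcomes. This limits the weight of the point, but Hypothesis II and the savings claims still depend on the count.

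**Conclusion.** The point holds in a limited form. The Specific Aims count measures gross reduction among patients already selected for CT. It does not support statements about overall imaging of blunt head injury victims, or the nationwide charge and radiation savings, unless rule-out-only use is assumed and stated. Under that assumption the derivation figure of 12.9% is correct as a gross reduction. Under two-way use with full adherence the net is 12.9% minus r × q, which is smaller whenever any un-imaged patient is positive, and its sign cannot be determined from the protocol. The break-even values show sensitivity to unknown inputs; they are not evidence that the saving is lost.

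The primary sensitivity outcome, the 368-case requirement and the no-missed-injury half of Hypothesis II are untouched. The change should be made because it alters what may be concluded about imaging, charges and radiation.

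**What to change.** 1. In the Specific Aims, state that the reduction estimate assumes the instrument is used only to omit scans. This describes what the estimate assumes and is not a rule for managing patients.
2. Label the count as gross reduction among patients already selected for CT.
3. Restrict the reduction part of Hypothesis II, and the charge and radiation figures, to that population, and align the Background's wording on overall imaging.
4. As a supportive analysis, report a net change at the site that records criteria on un-imaged patients: low-risk imaged minus criterion-positive un-imaged, divided by all blunt head injury patients there. Scale the un-imaged cohort to a count of all un-imaged patients at that site. State that the un-imaged data come from consenting patients at one centre and that clinicians were encouraged to image positive patients.
5. Reconcile section 4.3.9.2 (Pittsburgh) with sections 4.3.2.2, 4.3.3.1 and 4.3.4 and Appendix E (UCLA) on where un-imaged data are collected.

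Items 1 to 3 and 5 are changes of wording. Item 4 costs a modest extra analysis plus a count of un-imaged patients that the protocol does not now describe; the checks in Appendix E that all head injury patients are enrolled and surveyed could be extended to supply it. The headline saving will be claimed for a narrower population.
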